#### Missing data

Due to the design of the electronic CRF, within which a missing field is not permitted, the amount of missing data within an assessment visit should be kept to a minimum. However, missing data could still occur due to failure to attend for an assessment visit. Missing primary outcome data will be investigated through multiple imputation as a secondary sensitivity analysis of the primary outcome, should the missing data fall within the 20to 25% range.

#### Determination of sample size

The expected prevalence of healed ulcer in the control group and the treatment group is 40% and 55%, respectively, at 24 weeks. With α = 0.05 and β = 1-power (power 80%) and an estimated rate of dropouts of 30% a total of 531 patients of both genders will be included (to achieve 186 in each group completing the intervention phase). With 25% attrition, the number required is 496 (to achieve 186 in each group). The study will aim to recruit 500 patients and closely monitor the number of cases where the primary outcome data are missing. All secondary analyses will be interpreted with caution as the sample size calculation is based on the primary outcomes only. Internet-based treatment assignment will be determined by a computer-generated pseudo-random code using random permuted blocks of randomly varying size, created by the Nottingham CTU. Trial participants will be allocated with equal probability to each treatment arm with stratification by ulcer grade and ulcer size.

## Discussion

Ulcers of the heel constitute a major source of morbidity and cost, and there has hitherto been no specific therapy described. Recently, however, the use of lightweight fibreglass heel casts has been described and has been reported to improve both the incidence and speed of healing. The purpose of this trial is to document the efficacy of this intervention, as well as its cost, when compared to the use of defined criteria of best usual care.

The trial is randomised and while it is not possible to blind either the participant or their carer to the allocated arm of the study, the primary outcome measure (clinical healing) will be confirmed by a blinded observer. All non-clinical measures (including digital images of ulcer, measures of pain and discomfort) will be undertaken by blinded observers.

The study population is designed to be as inclusive as possible, with the aim of maximising the external validity of any findings. Thus, the intention is that as large a percentage as possible of people with diabetes complicated by ulceration of the heel could be included - including those with active infection, as well as those with all but the most severe peripheral arterial disease. This population is, however, one with multiple co-morbidities, a high expected incidence of unrelated illness and hospital admission and a poor overall life-expectancy. It is for this reason that a decision has been made to restrict safety measures to device effects. It is also for this reason that the sample size calculation allows for up to 30% attrition, and this is based on previous experience gained in conducting trials in this area.

While the primary outcome measure is that of healing, the trial includes a number of secondary outcome measures. Principal among these are rate of change in ulcer area - as an indication of the likelihood of eventual healing, and the experience of local pain and discomfort. While most foot ulcers in diabetes are typically painless, those on the heel are often the source of pain or other discomfort and experience reported by those who have used such casts in clinical practice is that reduction in local discomfort is often observed.

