#### Secondary endpoints

(i)*Ulcer-related outcomes*

Time to healing, change in ulcer area (measured by both acetate tracings and digital images analysed by using appropriate software to define area), infection, major and minor amputation, ulcer recurrence, secondary ulceration on either limb and adverse device effects (ADEs).(ii)*Patient-related outcomes*

Local pain (visual analogue scale; VAS), Euroqol-5D (EQ-5D), Cardiff Wound Impact Schedule (CWIS), hospital admission (relating primarily either to the heel ulcer or not), hospital length of stay and death.(iii)*Cost-effectiveness*

Cost-effectiveness will be assessed by developing a decision-analytic model to estimate costs and health outcomes, including percentage of healed ulcers and Quality Adjusted Life Years (QALYs) gained. Costs will be compared between the two groups using a bottom-up approach from the perspective of UK NHS and personal social services. Data relating to the costs of training professionals and the costs of heel casts and their application will be collected by discussions with relevant clinical and finance staff. Incremental cost-effectiveness and cost-utility ratios will be generated for a series of time horizons (including a lifetime perspective) that reflect management of patients with diabetic ulcers of the heel. The findings will be subjected to a series of one-way sensitivity analyses to determine the degree to which variation in parameter estimates affect the relative cost-effectiveness ratios. The results will be used to model the likely effects over the particular time horizons and costs and effects will be discounted at 3.5%. A probabilistic sensitivity analysis will be conducted to investigate the joint uncertainty in parameter values and cost-effectiveness acceptability curves will be generated. A budget impact analysis will be undertaken for 1-year and 5-year periods and will compare the costs to the health service of the use of heel casts in the management of ulcers of the heel in diabetes.

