**Table 1 Tab1:** **Fibreglass casts for heel ulcers in diabetes: trial profile**

	Screening visit	Visit 1 Randomisation	Visit 2	Visit 3	Visit 4	Visit 5	Visit 6	Visit 7	Visit 8	Visit 9	Visit 10	Visit 11	Visit 12	Visit 13
		Week 0	Week 2	Week 4	Week 6	Week 8	Week 10	Week 12	Week 14	Week 16	Week 18	Week 20	Week 22	Week 24
Check inclusion/exclusion criteria	**X**	**X**												
Information about study	**X**													
Informed consent	**X**													
Patient demographics		**X**												
ABPI		**X**												
Neuropathy		**X**												
Wound size by acetate tracing		**X**	**X**	**X**	**X**	**X**	**X**	**X**	**X**	**X**	**X**	**X**	**X**	**X**
Digital image after debridement		**X**	**X**	**X**	**X**	**X**	**X**	**X**	**X**	**X**	**X**	**X**	**X**	**X**
Cast applied if randomised to cast group		**X**	**X**	**X**	**X**	**X**	**X**	**X**	**X**	**X**	**X**	**X**	**X**	
Medication log		**X**	**X**	**X**	**X**	**X**	**X**	**X**	**X**	**X**	**X**	**X**	**X**	**X**
EQ-5D		**X**						**X**						**X**
CWIS		**X**						**X**						**X**
Pain VAS	**X**	**X**	**X**	**X**	**X**	**X**	**X**	**X**	**X**	**X**	**X**	**X**	**X**	**X**
Non-blinded Assessment			**X**	**X**	**X**	**X**		**X**	**X**	**X**	**X**	**X**	**X**	**X**
Collect health economic diary		**X**	**X**	**X**	**X**	**X**	**X**	**X**	**X**	**X**	**X**	**X**	**X**	**X**
Blinded assessment								**X**						**X**
							**Visit at which ulcer is judged healed**		**2 weeks after ulcer first judged healed**	**4 weeks after ulcer first judged healed**		**Visit 7 Week 12**		**Visit 13 Week 24**
Digital image after debridement							**X**		**X**	**X**		**X**		**X**
Cast applied if randomised to cast group							**X**		**X**	**X**		**X**		**X**
Medication log							**X**		**X**	**X**		**X**		**X**
EQ-5D												**X**		**X**
CWIS												**X**		**X**
Pain VAS							**X**		**X**	**X**		**X**		**X**
Non-blinded assessment							**X**		**X**	**X**		**X**		**X**
Collect health economic diary							**X**		**X**	**X**		**X**		**X**
Blinded assessment							**X**			**X**		**X**		**X**

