#### Randomisation

3.*Visits 2to 13 will be every 2 weeks* (*±4 days*) *to 24 weeks* (*visit 13*)

During each visit a check will be made for healing. If the ulcer is judged healed, it will be confirmed by blinded a clinician within 4 days. It will then be reviewed after two weeks (±4 days) weeks and 4 weeks (±4 days). If the ulcer is thought to remain healed at 4 weeks, healing will be confirmed once more by a blinded clinician. If the ulcer recurs during this period, the participant should return to the intervention phase of the study. If the ulcer does not recur, the participant should continue to collect data for health economic analysis and should be reviewed by the research staff at 12 and 24 weeks, assuming these dates have not already passed.

Other measures to be taken at different visits are charted in Table 1. The wound will be cleaned, debrided (when appropriate), traced and imaged at each visit before being redressed. Patient well-being and function will be documented by completion of EQ-5D and CWIS (weeks 12 (±1) and 24 (±2) only.

For participants randomised to the intervention group, a fibreglass heel cast will be replaced as necessary by trained personnel and the patient/carer will be given written and verbal instructions on its use.

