#### Secondary outcomes

Testing of the secondary outcome variables is exploratory and the results should mainly be used for exploratory purposes. On this basis, no adjustments for multiple testing will be performed.

The time to complete healing of the reference ulcer between the two randomized groups is an important secondary outcome and will be compared using survival analysis. Kaplan-Meier survival curves will be produced for the 2 groups and the median time to healing with 95% CI presented. Treatment effect will be explored using a Cox proportional hazards model including stratification factors (ulcer size and grade) initially. Participants’ heel ulcers that are not healed will be treated as censored and their date of trial exit, or date of last available assessment, or 168-day/trial cessation, as appropriate, will be used to calculate their duration in the trial. Hazard ratio with 95% CI will be given.

Final ulcer area will be analysed by treatment group for those who remain unhealed at the end of the study, using linear regression. As this exploratory analysis will include a subset of the participants, the analysis will be adjusting for baseline area, and any other variables that are found to be imbalanced at baseline (ANCOVA: on both an ITT and PP basis).

Ulcer related pain (measured on a VAS), will be analysed using linear regression and adjusting for baseline pain score, ulcer area, duration of ulcer, and ulcer type on both an ITT and PP basis.

Scores on standardised scales (EQ-5D) will be calculated in line with the guidelines provided by the original authors. The three domain scores will be calculated on the CWIS for each participant, in line with the standard instructions for use: descriptive statistics will be used to summarise these at each assessment. The standardised areas under the curve (area under the curve for each participant adjusted for the duration of available data) will be reported for both groups and compared using a Wilcoxon rank sum test.

*Secondary variables: Descriptive*

All other variables that will not be modelled formally will be considered descriptively. These are:(i)*Concomitant medications*

All concomitant medications will be listed descriptively by study treatment.(ii)Usual wound assessment and care requirements

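### The Discussion says pain is measured by blinded observers, but pain is a VAS reported by unblinded participants, and the unhealed-ulcer schedule marks a blinded assessment at only 2 of the 12 follow-up visits with a pain VAS

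*Protocol article*

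**What the plan says.** The Discussion takes up blinding in one short paragraph. It concedes that "it is not possible to blind either the participant or their carer to the allocated arm of the study", notes that clinical healing will be confirmed by a blinded observer, and then adds: "All non-clinical measures (including digital images of ulcer, measures of pain and discomfort) will be undertaken by blinded observers".

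Pain appears in four other places:

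- Secondary endpoints lists it among the patient-related outcomes: "Local pain (visual analogue scale; VAS").
- Secondary outcomes, under Statistical methods, compares it between arms: "Ulcer related pain (measured on a VAS), will be analysed using linear regression", with adjustment for baseline pain and ulcer characteristics, on both an ITT and a PP basis.
- The Discussion puts "the experience of local pain and discomfort" beside rate of change in ulcer area as principal among the secondary outcomes.
- Table 1 schedules the pain VAS at every visit. It has separate rows for "Non-blinded Assessment" and for blinded assessment.

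**The concern.** The two statements in the Discussion paragraph do not fit together for pain. A VAS for local pain records what the participant feels. If the participant knows whether a cast is being worn, the rating is made with that knowledge, and a blinded member of staff collecting the form does not remove it.

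At stake is how a pain result will be read. The device is visible and the comparator is usual care alone. The Background reports uncontrolled observations of prompt pain relief, and the Discussion says that reduced discomfort is often seen in practice. These are the conditions in which expectation can shift a subjective score without any effect of the device. If the report repeats the blinding statement, a reader may discount that explanation on the strength of a safeguard that the design does not provide.

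**Working it through.** **Step 1: who rates pain.** Inputs: the instrument is a VAS, it is classed as a patient-related outcome (Secondary endpoints), and the Discussion describes it as an experience. The document never uses the words self-rated or self-reported, so this is an inference, but no other rater is suggested anywhere. The Discussion says that participants cannot be blinded. Hence the number of pain scores given by a blinded rater is 0, at every visit.

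**Step 2: whether the schedule supports a blinded collector.** Suppose the sentence means only that blinded staff administer the scale. The Randomisation section gives the number of follow-up visits: "Visits 2to 13 will be every 2 weeks", that is, 13 − 2 + 1 = 12 visits, weeks 2 to 24. Counting the marks in Table 1:

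| Row | Unhealed-ulcer panel, visits 2 to 13 | Healed-ulcer panel |
|---|---|---|
| Pain VAS | 12 of 12 | 5 of 5 |
| Blinded assessment | 2 of 12 (weeks 12 and 24) | 4 of 5 |
| Non-blinded assessment | 11 of 12 (no mark at week 10) | 5 of 5 |

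Follow-up visits in the unhealed panel with a pain VAS and no blinded assessment: 12 − 2 = 10 of 12. In the healed panel the one time point with a pain VAS and no blinded assessment is the check two weeks after first healing. The missing non-blinded mark at week 10 may be an artefact of the table; nothing rests on it.

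**Step 3: what the blinded visits are for.** The note under Table 1 and the Randomisation section both give confirmation of healing as the reason for the blinded check at first healing and, in the latter section, four weeks later. Neither mentions pain.

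**Step 4: set side by side.** The Discussion claims blinded observers for all measures of pain. The design gives no blinded rater at any visit and, while the ulcer is unhealed, marks a blinded assessment at 2 of the 12 follow-up visits at which pain is scored.

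**Step 5: other participant-reported measures.** EQ-5D and CWIS are collected after baseline only at weeks 12 and 24, where a blinded assessment is marked, so the visit count does not touch them. Step 1 does, on the assumption that participants complete them.

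**The case against.** The best defence is that the trial is described only as observer-blind and that the disputed sentence speaks of who undertakes the measurement. The preceding sentence says openly that participants are not blinded, so a careful reader has the limitation in view. This softens the point but does not remove it: on that reading the schedule still lacks a blinded assessment at 10 of 12 visits, and a blinded collector does not blind a self-rating.

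A second defence is that secondary testing is labelled exploratory and that secondary analyses are to be interpreted with caution. Those labels are given for multiple testing and for a sample size based on the primary outcome. Neither corrects a statement about blinding.

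Other parts of the defence stand and set limits:

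- The 2 of 12 count belongs to the unhealed-ulcer panel. A reader might take it as applying to every participant; the healed-ulcer panel shows otherwise.
- Table 1 does not say who collects the VAS, so the count shows a conflict with the Discussion and is not a proven ceiling on blinded collection. The pain model names no time point either, so it is not shown that all 12 scores enter it.
- The Background reports earlier uncontrolled evidence and itself remarks that the apparent benefit seems large for so simple a device. It does not tell participants or readers to expect relief.
- A reader might infer that ulcer area is also wrongly handled, because the endpoint is "change in ulcer area (measured by both acetate tracings and digital images analysed by using appropriate software to define area") and most tracings fall at visits with no blinded assessment marked. The document does not support calling this an error. Which measurement is analysed may be left to the SAP, images can be read blind away from the visit, and the modelled final area falls, for completers, at week 24, where a blinded assessment is scheduled.

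**Conclusion.** The statement that pain is measured by blinded observers is wrong as written and should be corrected. Pain is rated by participants who know their allocation, so none of the scores is blinded in the sense that matters. On the unhealed-ulcer schedule, 10 of the 12 follow-up pain scores also fall at visits with no blinded assessment marked.

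The conclusion rests on one inference, that the participant completes the VAS, and on the marks in Table 1 as printed. It limits what can be concluded about a principal secondary outcome. A reader might go further and infer that the trial's blinding has failed or that a pain result will be biased by a known amount. Neither follows: healing, the primary endpoint, is confirmed by a blinded observer and is untouched, and the document gives no means of sizing an expectation effect. An unblinded pain outcome is unavoidable with this device; the fault lies in the description.

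**What to change.** - In the Discussion, limit the blinding claim to confirmation of healing and to the reading of digital images, and reconcile it with the assessment rows of Table 1.
- State that pain VAS, EQ-5D and CWIS are reported by participants who know their allocation.
- With the pain analysis under Secondary outcomes, state that a between-arm difference will be interpreted as an unblinded finding open to expectation bias.
- Optionally, for ulcer area, prefer the blinded reading of the images for analysis. They are already taken at the same visits as the tracings. This is a suggestion; no error is being corrected.

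The cost is wording only. No visit, assessment or extra data is needed, which matters because recruitment has closed. The downside is a more modest claim about pain and, if the option is taken up, an area analysis that depends on image quality.

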### Statistical analysis

Appropriate descriptive statistics will be presented for each variable. Two-sided statistical test will be performed and presented with exact *P*-values, with interval estimates constructed using 95% as the level of confidence.

Descriptive statistics, analytical methods and sample size considerations will be included. The study team together with the investigators will make the decisions regarding individual values belonging to a patient to be excluded from the analysis; for example, out of range values/values that cannot be objectively verified. The investigators will make the final decision regarding coding on the reason(s) for withdrawal. The safety population (SP) will comprise all randomised patients for the study

The intention-to-treat (ITT) population is defined as all subjects who were randomised. Given the study is based on a population with an expected high morbidity, the attrition rate will be monitored closely. If the missing primary outcome data fall within the 20 to 25% level, then ITT will be completed without imputation in the first instance and repeated with multiple imputation as a sensitivity analysis. ITT is equal to SP in this study. Once a participant has a healed wound, which is confirmed as ‘healed’, they will no longer participate in the intervention phase of the study, as they will have achieved the primary outcome. Such participants will be deemed to have completed their participation in the efficacy part of the study and their data will be included in the numbers ‘healed’ by 24 weeks.

Per protocol (PP) population is defined as a subset of ITT population that has completed the treatment period of maximum 24 weeks according to the protocol. The following will be regarded as a protocol violation necessitating exclusion from the PP analysis:

Failure to use the study intervention (fibreglass heel cast) as recommended for more than 7 consecutive days, or for more than a cumulative total of 14 days during the course of the 24-week studyOmission of more than one consecutive scheduled fortnightly assessment by the researcher, or omission of a total of 3 or more of these visits during the 24-week study

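### The 30% attrition allowance in the Discussion belongs to the 531-patient scenario; the adopted target of 500 keeps 186 per group only up to 25.6% attrition

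*Protocol article*

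**What the plan says.** Determination of sample size gives the planning assumptions: "The expected prevalence of healed ulcer in the control group and the treatment group is 40% and 55%, respectively, at 24 weeks". The section sets power at 80% and the significance level at 0.05. It then gives two recruitment totals for the same number of completers.

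- At 30% loss: "an estimated rate of dropouts of 30% a total of 531 patients of both genders will be included", the aim being "to achieve 186 in each group completing the intervention phase".
- At 25% loss: 496 patients, again for 186 per group.

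The same paragraph then sets the target: "The study will aim to recruit 500 patients". It adds that missing primary outcome data will be watched closely.

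The Discussion describes a population with much co-morbidity and poor life expectancy. It says that for this reason, and from previous experience of trials in the area, "the sample size calculation allows for up to 30% attrition".

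Trial status reports that 509 participants had been randomised when recruitment stopped.

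**The concern.** Two statements do not fit the adopted target. The sample size section says that 531 patients are to be included and, two sentences later, that the aim is 500. The Discussion then offers 30% attrition as the safeguard built in for a frail population, whereas 500 lies next to the 25% figure of 496 and well below 531.

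Attrition is a risk that the article itself stresses. Suppose that observed loss fell between about 26% and 30%. A reader who relied on the Discussion would conclude that the stated requirement was still met. A reader who worked from the sample size section would conclude that it was not. The article should give one answer.

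**Working it through.** **Inputs.** From Determination of sample size: healing 40% v 55% (difference d = 0.15), alpha 0.05, power 80%, arms "allocated with equal probability to each treatment arm", 186 completers per group, totals 531 and 496, target 500. From Statistical analysis: "Two-sided statistical test will be performed". From Trial status: 509 randomised. The article names no sample size formula, so the formula is inferred from which one returns 186.

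**Step 1: reproduce 186.** The mean proportion is 0.475.

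- Pooled-variance formula: n = [1.960 × √(2 × 0.475 × 0.525) + 0.8416 × √(0.40 × 0.60 + 0.55 × 0.45)]² / 0.15² = (1.3842 + 0.5876)² / 0.0225 = 172.8, so 173 per group.
- With continuity correction: n' = (n/4) × [1 + √(1 + 4/(n × d))]² = 43.2 × [1 + √(1 + 4/25.92)]² = 185.9, so **186 per group**, as stated.
- Other two-sided formulas without correction give about 170 (unpooled) and 173 (arcsine). One-sided versions give 136, or 150 with correction. None of these gives 186.

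**Step 2: reproduce the totals.** 2 × 186 = 372. Then 372/0.70 = 531.4 (stated 531) and 372/0.75 = 496 (stated 496). Both agree.

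**Step 3: attrition at which 372 completers remain.**

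- Target of 500: 1 − 372/500 = **25.6%**.
- 509 randomised: 1 − 372/509 = **26.9%**.

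**Step 4: what 30% attrition leaves.**

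- 500 × 0.70 = 350, or **175 per group**: 11 per group (22 in total) below the requirement.
- 509 × 0.70 = 356.3, or about 178 per group.

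**Step 5: power at those sizes.** Without correction, power = Φ[(0.15 × √n − 1.3842)/0.6982]. With correction, n is first replaced by its uncorrected equivalent, n × [1 − 1/(n × d)]². For 175 this is 175 × (1 − 1/26.25)² = 161.9.

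| Completers per group | Arises from | Continuity-corrected | Uncorrected |
|---|---|---|---|
| 186 | stated requirement | 80.0% | 82.8% |
| about 178 | 509 at 30% loss | 78.2% | 81.2% |
| 175 | 500 at 30% loss | **77.4%** | **80.5%** |

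By the uncorrected formula 173 per group (346 in total) suffice, and 500 would tolerate 1 − 346/500 = 30.8% attrition.

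**The case against.** The strongest reply is that the Discussion speaks of the calculation, not of the target, and the calculation does contain a 30% scenario. Read literally, the sentence is true. The sample size section also sets both scenarios side by side, so a careful reader can see that 500 goes with 25%. This stands as mitigation: nothing is concealed, and every figure in that section is arithmetically right. It does not remove the mismatch. The Discussion presents 30% as the protection that the trial has, and the sample size section still words 531 as the number to be included.

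A reader might go further and infer that the trial falls below 80% power at 30% attrition. The documents do not support that as a general statement. It holds only with the continuity correction. The primary analysis under Primary outcome is a logistic regression, to which such a correction does not belong, and the uncorrected figure at 175 per group is 80.5%.

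A reader might also infer that using a continuity correction, or not naming it, is an error. It is not. A conservative planning formula is legitimate, and an article commonly leaves the choice of formula to the full protocol.

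Finally, attrition is not the same as a missing primary outcome. Under Primary outcome, amputation of the target limb counts as not healed, and a confirmed healer who misses week 24 counts as healed. Some who leave early therefore still contribute, and 175 may understate the number analysable. That point stands, but the plan makes the same simplification when it counts completers of the intervention phase.

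**Conclusion.** The point holds as an inconsistency in a stated design property. By the article's own requirement of 186 per group, the target of 500 allows for 25.6% attrition, not 30%, and the 509 randomised allow for 26.9%. At 30%, 500 gives 175 per group, 11 short.

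The consequence for power is small: 2.6 percentage points below 80% by the formula that reproduces 186, and no shortfall by the uncorrected formula. With 509 the corresponding figures are 78.2% and 81.2%.

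These results assume 40% v 55% healing, two-sided 0.05, equal allocation, attrition spread evenly over the arms, and every lost participant counted as not analysable. The continuity correction is an inference from the exact match to 186. No recruitment decision, analysis or trial conclusion turns on the point.

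**What to change.** Two changes of wording:

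1. **Discussion.** Replace the 30% claim with a statement about the adopted target: 500 patients keep the required 186 per group up to about 25% attrition; at 30% attrition 175 per group would remain, with power of about 77% by the planning formula and about 80% without continuity correction.
2. **Determination of sample size.** Mark 531 as the 30% scenario that was considered and not adopted, so that 500 stands as the only target.

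The cost is a few lines of text. The stated tolerance becomes slightly less favourable (about 25% rather than 30%), and recruitment and the planned analyses stay as they are.
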